### Note on Timing

All solicited and unsolicited AEs occurring through Day 7 post-vaccination will be assessed and recorded. All AEs that meet the criteria for an SAE and that occur through 6 months post-vaccination will be assessed and recorded.

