## TRIAL OVERVIEW

A randomized, controlled, Phase II trial will test Vi-TCV co-administration with vaccinations routinely given at 9 and 15 months of age in Burkina Faso. Our aim is to assess the safety and immunogenicity of Vi-TCV when co-administered with vaccinations routinely given to children at both 9 and 15 months of age in Burkina Faso. The Vi-TCV vaccine or an inactivated poliovirus vaccine (IPV) will be administered. Children 9–11 months of age will be randomized 1:1 to Vi-TCV or IPV; children 15–23 months of age will be randomized 1:1:1 to Vi-TCV + MCV-A, Vi-TCV + IPV with delayed MCV-A, or MCV-A + IPV. We will use block randomization with varying block sizes from 6–12. Our study objectives and endpoints are listed in Table 1.

**Table 1. T1:** Primary, Secondary, and Exploratory Objectives and Endpoints

	Objectives	Endpoints
**Primary**	To assess the safety of Vi-TCV when co-administered with Expanded Program on Immunization vaccines among children 9–11 months of age and 15–23 months of age in Burkina Faso.	1. Proportion of participants who develop adverse events in the first 30 minutes after vaccination and for 7 days after vaccination. 2. Proportion of participants who experience SAEs within 6 months of vaccination, in all participants. 3. Proportion of participants who experience other, non-serious adverse events up to 28 days following vaccination.
**Secondary**	1. To assess the immunogenicity of YFV when given with and without Vi-TCV in children 9–11 months of age. 2. To assess the immunogenicity of MCV-A when given with and without Vi-TCV in children 15–23 months of age. 3. To assess the immunogenicity of Vi-TCV when given with YFV in children 9–11 months of age. 4. To assess the immunogenicity of Vi-TCV when given with and without MCV-A in children 15–23 months of age.	1. Immunogenicity of YFV: yellow fever plaque reduction neutralization test at Days 0 and 28 in infants 9–11 months of age. 2. Immunogenicity of MCV-A: serum bactericidal antibody assay against *Neisseria meningitidis* serogroup A at Days 0 and 28 in children 15–23 months of age. 3. Immunogenicity of Vi-TCV when given with YFV: anti-Vi IgG antibody titer, as measured by ELISA at Days 0 and 28 in infants 9–11 months of age. 4. Immunogenicity of Vi-TCV when given with and without MCV-A: anti-Vi IgG antibody titer, as measured by ELISA at Days 0 and 28 in infants 9–11 months of age.

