We will measure anti-Vi immunoglobulin G (IgG) antibody responses using the VaccZyme Salmonella typhi Vi IgG enzyme-linked immunosorbent assay commercial kit (The Binding Site Group Ltd, Birmingham, UK). Antibody titers will be expressed as enzyme-linked immunosorbent assay units per milliliter (U/mL). Both anti-Vi IgG antibody geometric mean titers and seroconversion, defined as a 4-fold or greater rise in anti-Vi antibody titers from baseline, will be calculated per group. The difference in geometric mean titers between the 2 groups will be compared using a 2-sample Student *t* test on log-transformed titers or a Mann-Whitney U test, as appropriate. The difference in the percentages of participants who seroconverted between the 2 groups will be compared using the Pearson’s chi-square test or Fisher’s exact test, as appropriate.

Participants in both cohorts will have home or clinic visits on Days 3 and 7 following vaccination, for local and systemic adverse event (AE) capture. Non-serious AEs will be assessed up to Day 28. Serious adverse events (SAEs) will be captured throughout the study follow-up.

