## ADVERSE EVENTS

### Immediate Reactions

All participants will be observed for immediate reactions for 30 minutes after vaccination. Immediate reactions will be assessed by a study physician or appropriately trained medical staff member, and recorded on the appropriate case report form (CRF).

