### Definition of Adverse Event

An AE is any untoward medical occurrence in a participant to whom Vi-TCV or IPV has been administered, including occurrences that are and are not caused by or related to the vaccine. All AEs related to study vaccination that are reported by telephone or by home or clinic visits in the first 7 days after vaccination will be recorded, including the event description, the date of onset, the resolution, the level of severity, an assessment of relatedness to the study, and the outcome.

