## DISCUSSION

This randomized, controlled clinical trial among infants and young children in Ouagadougou, Burkina Faso, will be the first in West Africa to test the pre-qualified Typbar-TCV. The study will provide the first information on co-administration of this vaccine with YFV and MCV-A, as recommended by the WHO. The rationale for the 3 arms in the older children is that both MCV-A and TCV contain tetanus toxoid as the carrier protein: thus, our study design allows us to carefully assess reactogenicity when those vaccines are given alone or together, and evaluate any effect on the antibody responses that might occur with a shared carrier protein. Such a phenomenon was noted with *Haemophilus Influenzae* Type b vaccines [18] and is thought to occur due to interference by a common protein carrier with common immunogenic epitopes [19]. We did not include an assessment of measles and rubella antibody responses, since this has been previously tested and we have attempted to minimize blood collection volumes in these young children.

Malaria parasitemia is prevalent among young children in Burkina Faso. We will test for *P. falciparum* parasitemia at Day 0 to evaluate the potential effect on the immunogenicity of Typbar-TCV and of the other vaccines administered.

**Table 4. T4:** Trial Schedule of Events. Abbreviations: AE, adverse event; SAE, serious adverse event.

Study Visit Type	Recruitment	Screening	Eligibility, enrollment, vaccination	Follow up	Follow up	Follow up	Follow up	Early termination
Study Visit Number		V00	V01	V02	V03	V04	V05	
Study Time point			D0	D3	D7±1	D28±3	D180±7	
Study introduction, recruiting	X	X^a^	X^a^					
Obtain informed consent		X	X^a,b^					
Review eligibility criteria		X	X^a,c^					
Review medical history		X	X^a,c^	X^c^	X^c^	X^c^	X^c^	X^c^
Review concomitant meds		X	X^a,c^	X^c^	X^c^	X^c^	X^c^	X^c^
Review vaccination history		X	X^a,c^	X^c^	X^c^	X^c^		X^c^
Axillary temperature^d^		X	X^e^			X		X
Height and weight and Middle Upper Arm Circumference (MUAC)		X	X^e^				X	X
Targeted physical exam		X^˚^	X^a,c,e,˚^			X^c,˚^		X^c,˚^
Vaccination			X			X^f^		
30-min post-vaccination evaluation			X					
Post-vaccination reactogenicity assessment				X	X			X
Venous blood collection for immunogenicity			X^e,g^			Xg		X^g^
Venous blood collection for malaria parasitemia			X^e^					
Assess and record SAES			X^h^	X	X	X	X	X
Assess and record solicited AEs			X^h^	X	X			X^i^

^a^If not performed at previous visit.

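### Primary endpoint 3 counts non-serious adverse events to Day 28, but the recording rules describe collection only through Day 7, so collection in Days 8–28 is contradictory

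*Protocol article*

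**What the plan says.** Two places in the protocol article set a 28-day window for non-serious AEs:

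- Trial Overview, Table 1, primary endpoint 3: "Proportion of participants who experience other, non-serious adverse events up to 28 days following vaccination".
- Methods: "Non-serious AEs will be assessed up to Day 28".

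Four places describe what is recorded and when:

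- Note on Timing: "All solicited and unsolicited AEs occurring through Day 7 post-vaccination will be assessed and recorded". The sentence after it deals only with serious adverse events (SAEs): "All AEs that meet the criteria for an SAE and that occur through 6 months post-vaccination will be assessed and recorded".
- Definition of Adverse Event: what is to be recorded is "All AEs related to study vaccination that are reported by telephone or by home or clinic visits in the first 7 days after vaccination". The sentence just before it defines an AE as any untoward occurrence, whether or not the vaccine caused it.
- Follow-up: unsolicited AEs are tied to the Day 3 and Day 7 visits. The Day 28 visit is described through unblinding of the older cohort and blood sampling, with no mention of AEs. Illnesses seen at unscheduled visits are to be documented as AEs, with no day limit.
- Table 4 has two rows for recording AEs. The SAE row is marked at every visit from D0 to D180 and at early termination. The other row, "Assess and record solicited AEs", is marked at D0, D3 and D7, and at early termination only within 7 days of vaccination. No row covers unsolicited or other non-serious AEs at any visit.

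**The concern.** Safety is the only primary objective, and endpoint 3 is one of its three endpoints. Site staff work from the recording rules and the visit schedule, not from the endpoint table. Staff who follow the Note on Timing have no instruction to record a non-serious event that starts on Day 12. Staff who follow the Methods sentence would record it. The two readings give different data for the same endpoint, and events not written down at the time cannot be reliably recovered at analysis.

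The relatedness wording raises a second problem. If a causality judgement decides whether an event is recorded at all, the endpoint stops being a plain count that can be compared between randomized groups. An imbalance made up of events each judged unrelated would not appear.

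**Working it through.** **No figure to reproduce for endpoint 3.** The article states no expected proportion or power for it. The nearest figure is the Table 3 power for reactogenicity: 45 per group, 10% against 33%, two-sided 5% test with unpooled variance.

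- Standard error = √(0.10 × 0.90/45 + 0.33 × 0.67/45) = √(0.3111/45) = 0.0831
- Power = Φ(0.23/0.0831 − 1.96) = Φ(0.81) ≈ 79%, against 80% stated

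That agrees within rounding. It concerns solicited systemic events of grade 2 or higher over 7 days, so the present point does not touch it.

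**Matching the rules to the primary endpoints in Table 1.**

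| Primary endpoint | Window | Rule in Note on Timing | Row in Table 4 |
|---|---|---|---|
| 1. AEs after vaccination | 30 minutes and 7 days | Day 7 | Solicited AEs to D7; 30-minute evaluation |
| 2. SAEs | 6 months | 6 months | SAEs to D180 |
| 3. Other non-serious AEs | 28 days | None beyond Day 7 | None |

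The Note on Timing serves endpoints 1 and 2. Endpoint 3 has no matching rule there and no row in the schedule.

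**Share of the window.** Days 8–28 are 28 − 7 = 21 days, and 21/28 = 75% of the calendar window. This does not say what share of events would be missed.

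**Illustration of the undercount.** Assume a constant event rate over 28 days and nothing recorded after Day 7. If P is the true 28-day proportion with at least one event, the proportion recorded is 1 − (1 − P)^(7/28).

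| True 28-day proportion (assumed) | Recorded if collection stops at Day 7 |
|---|---|
| 10% | 2.6% |
| 30% | 8.5% |
| 50% | 16% |
| 70% | 26% |

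The article gives no event rate, so these inputs are assumptions. If events cluster soon after vaccination the loss is smaller. Any capture at unscheduled visits or at Day 28 also reduces it.

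**Relatedness.** The Definition of Adverse Event section conflicts with its own preceding sentence, which includes unrelated events, and with the Note on Timing, which says all events. It also lists an assessment of relatedness among the items recorded for each event, which is hard to square with relatedness as the condition for entry.

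**The case against.** The strongest reply is that the Methods do state assessment of non-serious AEs up to Day 28, and that two collection routes run past Day 7. Illnesses at unscheduled visits are documented as AEs without a day limit. Every child also has a medical history and concomitant medication review at Day 28, with a targeted examination if indicated. The Note on Timing does not forbid later recording. Table 4 omits unsolicited AEs even at Days 3 and 7, where the Follow-up section says they are recorded, so the missing row cannot by itself show that nothing is collected at Day 28. The article is also a condensation of a fuller protocol.

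Much of this stands. A reader might infer that endpoint 3 cannot be produced at all, or that three quarters of its events would be lost. The documents support neither: the Methods sentence would yield the endpoint if sites followed it, and 75% is calendar arithmetic.

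It does not remove the contradiction. Unscheduled visits capture only children whose families sought care. The Day 28 history review has no stated step for recording AEs, and it falls at the visit where Cohort 2 (150 of the 250 children) is unblinded. Condensation explains missing detail, but here the article states two windows, and its schedule gives no support to the longer one.

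On relatedness, one may fairly say that the phrase is loose drafting and that assessors are blinded until at least Day 28, so the judgement would not be informed by group. A reader might infer that the endpoint will definitely be filtered on relatedness. The text does not establish that, since two other sections apply no filter. The sentence is still an instruction about what to record, and it conflicts with the definition above it.

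No power statement in Table 3 depends on endpoint 3.

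**Conclusion.** The point holds as an internal contradiction affecting one of three primary endpoints and all 250 planned children. Table 1 and the Methods set Day 28. The Note on Timing and the Definition of Adverse Event section set Day 7, the latter with a relatedness condition, and Table 4 has no row for these events.

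The consequence depends on which text sites follow. If the Methods sentence governs, the endpoint is obtained as intended. If the recording rules are followed literally, it is undercounted, or Days 8–28 depend on who sought care and on what a history review happens to bring out. The illustrated undercount rests on an assumed constant rate and no capture after Day 7, and should be read as an upper-end example. The contradiction itself rests on no assumption. The full protocol may already resolve it, but the article as written does not. It should be corrected because the lost data could not be recovered later.

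A separate and minor point concerns Group 3. Table 4 gives this group a vaccination at Day 28 but marks the 30-minute evaluation at V01 only, while the Immediate Reactions section says "All participants will be observed for immediate reactions for 30 minutes after vaccination". That sentence may mean Day 0 alone. It has no bearing on collection in Days 8–28.

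**What to change.** 1. In the Note on Timing, state that all non-serious AEs, whatever their relationship to vaccine, are recorded from Day 0 through the Day 28 visit, with solicited reactions through Day 7. The SAE sentence stays.
2. In the Definition of Adverse Event section, remove relatedness to study vaccination as a condition for recording and align the 7-day limit with item 1. Keep relatedness as an attribute recorded for each event.
3. Add a Table 4 row for assessing and recording unsolicited AEs at D0, D3, D7, D28 and early termination.
4. Separately, reconcile Table 4 with the Immediate Reactions section for Group 3's Day 28 vaccination.

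The cost of items 1 to 3 is two sentences, one table row and one CRF page. The Day 28 clinic visit and its history review are already planned for every child, so no visit or blood sample is added. The sample size is unaffected.

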### Follow-up

Follow-up visits may be either routine or unscheduled. Routine visits will occur on Days 3, 7, 28, and 180. On Days 3 and 7 following vaccination, participants will be asked to return to the study clinic to assess reactogenicity. During these visits, solicited and unsolicited AEs will be recorded. Alternatively, these visits may be conducted in the home. On Day 28 following vaccination, participants will be asked to return to the study clinic for a follow-up visit. During this visit, the treatment groups in the 15–23-month-old cohort will be unblinded, participants will have approximately 3–5 mL of blood drawn to measure the Vi antibody responses for typhoid (all age groups), measure the TT serum IgG antibody levels (all age groups), and conduct the yellow fever plaque reduction neutralization testing (9–11-month-old group only) or measure the meningococcal A serum bactericidal antibody titers (15–23-month-old group only), which will be used for the primary and secondary objectives, as listed. Participants will have their final visit on Day 180, when interim SAEs will be recorded.

During unscheduled visits, participants will undergo standard procedures for the evaluation and treatment of illness, as defined by the Ministry of Health. Illnesses and other medical issues will be documented as AEs in participant records, and their seriousness, severity, relationship to the study product, and expectedness will be recorded.

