### Solicited Local and Systemic Reactions

On Day 3, participants will be assessed for local and systemic reactions and will be asked about any events after vaccination on Day 0 and any current symptoms; on Day 7, participants will be assessed for local and systemic reactions and will be asked about current symptoms. Using a standardized data collection instrument, the following local and systemic reactions will be documented and graded on predefined scales, based on a functional assessment or the magnitude of the reaction: fever, injection site pain/tenderness, swelling, erythema, and irritability.

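### Table 4 lets the visits that close the primary safety windows fall before those windows end (Day 6 for 7 days, Day 173 for 6 months); the loss is small and equal across arms, but avoidable

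*Protocol article*

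**What the plan says.** **Endpoints.** Table 1 of the protocol article gives the first primary endpoint as "Proportion of participants who develop adverse events in the first 30 minutes after vaccination and for 7 days after vaccination" and the second as "Proportion of participants who experience SAEs within 6 months of vaccination, in all participants". The third covers other non-serious AEs up to 28 days.

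**Recording promise.** The Note on Timing states "All solicited and unsolicited AEs occurring through Day 7 post-vaccination will be assessed and recorded" and, for serious events, "All AEs that meet the criteria for an SAE and that occur through 6 months post-vaccination will be assessed and recorded".

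**Visit windows.** Table 4 sets V03 at D7±1 (Day 6 to 8), V04 at D28±3 (Day 25 to 31) and V05 at D180±7 (Day 173 to 187).

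**Contacts that collect events.** The Table 4 row "Assess and record solicited AEs" is marked at D0, D3 and D7, and at early termination only within 7 days of vaccination. It is not marked at D28. For SAEs, the Follow-up section says "Participants will have their final visit on Day 180, when interim SAEs will be recorded". The section on solicited reactions says that "on Day 7, participants will be assessed for local and systemic reactions and will be asked about current symptoms".

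**Other routes.** The definition of an AE adds "All AEs related to study vaccination that are reported by telephone or by home or clinic visits in the first 7 days". Methods has non-serious AEs assessed up to Day 28, and Follow-up has illnesses seen at unscheduled visits documented as AEs.

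**The concern.** A symmetric window suits a blood sample. It suits a visit that closes an event-counting period less well. If the visit is late, events after the limit can be removed by onset date, which the AE definition says is recorded. If it is early, the days between the visit and the limit have no structured collection.

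A visit on Day 6 or Day 173 complies fully with Table 4, yet it leaves the promise in the Note on Timing unmet. Safety is the trial's only primary objective and its endpoints are proportions with an event by a fixed time. A child seen early and reported as event-free has therefore been observed for less than the stated period, and the absolute proportions come out slightly low.

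**Working it through.** **1. The plan's own figure.** Table 3 gives 80% power for 10% vs 33% with 45 per arm (two-sided 5% z-test, unpooled variance).

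- Power = Φ(|p1 − p2| / √[(p1q1 + p2q2)/n] − 1.96)
- = Φ(0.23 / √[(0.09 + 0.2211)/45] − 1.96) = Φ(2.766 − 1.96) = 0.790

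This reproduces the stated 80% to rounding. The sample size is not in dispute.

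**2. Days left uncovered.** Assume each permitted visit day is equally likely.

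| Visit | Permitted days | Endpoint limit | Share early | Mean loss |
|---|---|---|---|---|
| V03 | 6–8 | Day 7 | 1/3 | 1/3 day; (1/3)/7 = 4.8% |
| V04 | 25–31 | Day 28 | 3/7 | (3+2+1)/7 = 0.86 day; 0.86/28 = 3.1% |
| V05 | 173–187 | Day 180 | 7/15 | (7+6+5+4+3+2+1)/15 = 28/15 = 1.87 days; 1.87/180 = 1.0% |

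The worst case for a single child is 1 of 7 days at V03 and 7 of 180 days (3.9%) at V05. The V03 figure also assumes that the visit covers every day since Day 3, whereas the text has it ask only about current symptoms.

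**3. Effect on the 7-day comparison.** Assume a constant hazard, so that a child seen on Day 6 has p′ = 1 − (1 − p)^(6/7).

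- Every child seen on Day 6: 10% becomes 8.6%, 33% becomes 29.1%, and power is 0.728.
- Half seen on Day 6: 9.3% vs 31.0%, power 0.760.
- A quarter seen on Day 6: 9.7% vs 32.0%, power 0.775.

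An even spread (one third early) lies between the last two. If reactions come early and only 1% start on the last day, power is 0.784 even with every child seen early.

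**4. Effect on SAEs.** The protocol article gives no SAE rate, so 1% to 5% over 180 days is assumed. If all 250 children were seen on Day 173, the expected number with a missed SAE is 250 × [p − (1 − (1 − p)^(173/180))], which is 0.10 at 1% and 0.47 at 5%. An even spread scales this by about 1.87/7, giving 0.03 to 0.13 children.

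**The case against.** The strongest reply has four parts.

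- **Day 7 events have other routes.** A reader might infer from Table 4 that an early V03 loses Day 7 for good. The text does not support that. Non-serious AEs are assessed to Day 28, V04 reviews medical history, related AEs can be reported by telephone in the first 7 days, and unscheduled visits generate AE records. This stands for Day 7: what is missed is the structured reaction check, not every chance of recording the event. It does not cover the days after V05, which no scheduled contact follows.
- **The visit window is not the largest gap at V03.** Because that visit asks about current symptoms, a reaction that began and resolved between Day 3 and Day 7 can be missed even at an on-time visit. Moving the window alone would not cure this, and a Day 8 visit would need a recall question to cover Day 7. This stands and shapes the fix.
- **The size depends on the calendar.** A reader might count 6 months as about 183 days and conclude that 10 of 15 V05 days fall short. The trial places its 6-month visit at Day 180, so the loss belongs against Day 180. The difference shows only that 6 months should be defined in days.
- **Handling of short follow-up may be settled elsewhere.** The Analysis section includes all follow-up time in the intention-to-treat population and leaves detail to an analysis plan that is not shown. It would be wrong to assert that early visits are analysed without allowance for time at risk. An analysis can allow for unobserved days, but it cannot observe them.

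**Conclusion.** The mismatch between the visit windows and the recording promise is real. It affects the 7-day and 6-month primary safety endpoints, and the 28-day endpoint has the same structure. The consequence is minor. With evenly spread visits, about one third of V03 visits fall a day early, and V05 loses 1.87 days on average, about 1% of 180 days. At assumed SAE rates of 1% to 5%, well under one child with an SAE would be expected to be missed. Absolute incidence is slightly understated.

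A reader might infer that the comparison between arms is biased or that the sample size is wrong. Neither follows. The windows are identical in every arm, and the stated power reproduces. The absence of bias assumes that visit timing does not depend on arm. Randomization and blinding support this to Day 28; after Cohort 2 is unblinded on Day 28, it is an assumption for V05 in that cohort.

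This is worth correcting because it is cheap and because days not asked about cannot be recovered in the analysis.

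**What to change.** 1. In Table 4, make the closing windows one-sided: for example, V03 on Day 7 to Day 8 and V05 on Day 180 to Day 194.
2. Apply the same principle to the 28-day endpoint, with the contact that closes non-serious AE collection on Day 28 or later. V04 also carries the blood sample and the Group 3 MCV-A dose, so the investigators need to check any change there against those procedures.
3. Define 6 months as Day 180 in Table 1 and the Note on Timing.
4. Have V03 ask about all reactions since the Day 3 visit, with onset dates, and not only current symptoms.
5. Count an event towards an endpoint only if its onset lies within the endpoint window, so that late visits add nothing.

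Shortening the SAE endpoint to Day 173, a day every completer reaches, is not recommended. It would discard up to 7 days for every child to avoid a mean loss under 2 days.

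**Cost.** No added visits or blood draws. V03 has two permitted days instead of three. V05 keeps 15 permitted days, but its latest date moves from Day 187 to Day 194, so the last visit falls up to a week later for some children.
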